### Sample size calculation

The sample size calculation is designed to account primarily for intervention level outcomes. Powering the study in this way will also account statistically for appropriate outcomes for screening approach and screening method. The primary outcome for this study is the proportion of offenders who are consuming alcohol within recommended levels at 6 and 12 month follow-up. Recent meta-analysis [19] suggests that the difference between brief intervention and control is of the order 13%, 5% reduction in the control group and 18% in the brief intervention group. In order to detect a difference of this magnitude at the 5% significance level with 80% power, for a 2-sided test, requires 109 offenders in each of the 3 groups, a total of 327. Our experience with other multi-centre randomised controlled trials of interventions for alcohol use disorders suggests that with assiduous follow-up the potential loss to follow-up across groups is of the order 25%. Taking this loss into accounts inflates the sample required to 145 in each group, a total of 435 offenders.

The proposed study involves a cluster design and requires a statistical adjustment to account for any potential cluster effect. The literature is unclear regarding an appropriate estimation of an intra-class correlation coefficient in this population. Our experience leads us to assume the ICC should be similar to primary care correlation coefficients, 0.04. Assuming a cluster size of the order 3 offenders this inflates the sample size calculation by a factor of 1.1 requiring 160 offenders in each group, a total of 480, with an expectation that at least 365 will be followed up at 12 months.

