### Brief lifestyle counselling

OMs randomised to deliver Brief Lifestyle Counseling, will be trained to screen eligible offenders for hazardous or harmful drinking. Offenders who screen positive and provide consent to participate in the study will complete the baseline questionnaire and will then receive up to five minutes of simple structured brief advice from trained OMS using the SIPS Brief Advice tool "Brief advice about alcohol risk". Offenders in this condition will also receive a Client Information Leaflet (CIL) at the end of the brief advice. OMs will also be trained to refer offenders to an AHW, by making an appointment usually the following day or as soon as possible after probation attendance. The AHW will be experienced in carrying out alcohol assessment and brief interventions. The AHW will deliver a 20 minute brief lifestyle counseling intervention to offenders who attend the appointment at the probation office, using the SIPS Brief Lifestyle Counselling (BLC) Tool which has been developed for the purpose of the SIPS programme. It is based on the "How much is too much?" Extended Brief Intervention tool developed as part of the UK version of the Drink-Less BI programme [31] from a prototype used as part of a World Health Organisation collaborative study on alcohol screening and brief intervention [32].

All intervention tools and protocols are available from the SIPS study website http://www.sips.iop.kcl.ac.uk.

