### Training of staff to deliver brief lifestyle counselling

AHWs will be recruited to deliver the BLC within the participating probation offices. Staff recruited will, as a minimum, possess; a relevant professional qualification, a diploma in drug and/or alcohol studies or equivalent, 5 years post-qualifying experience with a minimum 2 years in an alcohol or drug speciality, prior knowledge and understanding of psychological interventions including motivational interviewing.

All AHW's will receive formal training and supervision from the point of recruitment. Training will be based upon the previous work of Rollnick et al [33] in addition to experiences from an earlier trial of screening and brief interventions [34]. The training will comprise of four main elements; orientation to the relevant OM, taught workshops, tape recorded simulated consultations with trained actors and ongoing clinical supervision provided by experienced senior clinicians.

The simulated consultations will be recorded and rated by three independent clinical assessors. The AHW will be assessed for adherence to the BLC protocol in addition to their behaviour and skills using the Behaviour Change Counselling Index (BECCI) [35]. Assessors will submit BECCI ratings, comments and supervision points for each consultation. This information will support clinical supervision and training until the AHW reaches a required standard of practice agreed by an independent clinical assessor.

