### Planned analysis

As the study is pragmatic in design, the planned analysis will be by intention to treat. The primary outcome is dichotomous in nature, drinking within or above recommended levels, and will be analysed with logistic regression adjusting for all known prognostic factors; data will be presented as odds ratios and their corresponding confidence intervals. Secondary analyses will be undertaken using the appropriate method for the outcomes, controlling where appropriate for intake values and other known prognostic variables using analysis of covariance.

Due to the nested factorial nature of the study, we will use multi-level modelling to explore potential interactions between each of the levels nested within the trial (screening method and intervention). Offender manager and offender factors will be utilised as part of regression model to explore possible prognostic factors that impact on outcome. Interaction analysis will explore any possible interactions between site and offender characteristics and outcome.

The efficacy of interventions will be explored using a per protocol approach to the analysis. A sub-group, of those who received their allocated treatment will be utilised for this analysis.

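### The sample size allows for clustering by Offender Manager only, so the 80% power for brief lifestyle counselling v leaflet is supported only if clustering by Alcohol Health Worker is negligible

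*Protocol article*

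**What the plan says.** All of this is in the Protocol article.

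- **Sample size calculation.** The planning difference is stated as follows: "the difference between brief intervention and control is of the order 13%, 5% reduction in the control group and 18% in the brief intervention group". Detecting it "at the 5% significance level with 80% power, for a 2-sided test, requires 109 offenders in each of the 3 groups". On attrition, "the potential loss to follow-up across groups is of the order 25" per cent. On clustering, the authors "assume the ICC should be similar to primary care correlation coefficients, 0.04", and then: "Assuming a cluster size of the order 3 offenders this inflates the sample size calculation by a factor of 1.1 requiring 160 offenders in each" arm. The ICC is not tied to a named level. The only cluster described anywhere is the OM, which is the unit of randomisation (Design).
- **Brief lifestyle counselling.** OMs in this arm give the short structured advice and the leaflet themselves. In addition, "OMs will also be trained to refer offenders to an AHW, by making an appointment usually the following day or as soon as possible". The AHW then gives the 20-minute session to those who attend.
- **Training of staff to deliver brief lifestyle counselling.** "AHWs will be recruited to deliver the BLC within the participating probation offices". These are qualified specialists, individually rated and supervised to a required standard. Their number, their caseload and the OMs each one serves are not given.
- **Planned analysis.** The primary outcome is analysed by logistic regression. Multi-level modelling is mentioned as a way to "explore potential interactions between each of the levels nested within the trial (screening method and intervention"). No provider level is named.

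**The concern.** In the leaflet and brief advice arms the OM delivers the whole intervention, so clustering by OM covers the provider effect. In BLC a second provider delivers the component that sets the arm apart. Clients of different OMs who see the same AHW share that counsellor's skill and style, so their outcomes may be correlated across OMs. This is a partially nested design, with an extra level in one arm only. An OM effect does not absorb it, because two OMs who refer to the same AHW would still be treated as independent.

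The first study hypothesis (BLC v brief advice) and half of the second (BLC v leaflet) depend on this arm, and the Economic evaluation compares control with the AHW condition. If outcomes vary between AHWs and the level is left out, standard errors for both contrasts are too small, and the effect of a few good counsellors could be read as an effect of the intervention. For BLC v leaflet the effective sample size would also be below the one behind the stated 80%. Brief advice v leaflet is unaffected.

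**Working it through.** **Reproducing the plan's figures.** For 5% v 18%, two-sided 5%, 80% power, the two-proportion formula with pooled null variance gives 93.3 per arm without continuity correction and 108.2 with it. The printed 109 is therefore the continuity-corrected figure. Then 109/0.75 = 145.3 and 145 × 1.1 = 159.5, giving 160. The chain reproduces.

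**Inputs.**
- From the article: 160 per arm less 25% = 120 analysed; 160/32 = 5 clients recruited per OM, or 3.75 after loss. OM design effect = 1 + 2.75 × 0.04 = 1.11, in line with the printed 1.1.
- Assumed, because the article gives none of them: number of AHWs K, AHW-level ICC ρ, and share a of BLC clients who attend the AHW.

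**Formulas.**
- Clients per AHW: M = 120a/K.
- Design effect in BLC: D = 1.11 + a(M − 1)ρ.
- Effective n: 120/1.11 = 108.1 in the leaflet arm; 120/D in BLC.
- Power = Φ[(0.13 − c − 1.96 × SE0)/SE1], where c is half the sum of the reciprocals of the two effective sizes, SE0 uses the pooled proportion and SE1 the separate proportions.

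**OM clustering only.** D = 1.11 in both arms gives 80.0%, so there is no reserve. (The article's expected 365 followed up, about 122 per arm, adds less than one point.)

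**One case in full: K = 9, ρ = 0.04, all attend.** M = 13.3. D = 1.11 + 12.33 × 0.04 = 1.60. Effective n in BLC = 74.8. Pooled proportion 0.103, SE0 = 0.0457, SE1 = 0.0491, c = 0.0113. Then (0.13 − 0.0113 − 1.96 × 0.0457)/0.0491 = 0.59, and power is 72.3%.

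**BLC v leaflet power (%), OM term kept, AHW term added:**

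| AHWs | Attending | Clients per AHW | ρ = 0.01 | ρ = 0.02 | ρ = 0.04 |
|---|---|---|---|---|---|
| 9 | all | 13.3 | 77.9 | 75.9 | 72.3 |
| 3 | all | 40 | 73.8 | 68.5 | 60.1 |
| 9 | half | 6.7 | 79.5 | 79.0 | 78.1 |
| 3 | half | 20 | 78.4 | 76.8 | 73.9 |

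Basing the continuity correction on the actual 120 per arm moves these by 0 to 3 points (80.6% with OM clustering only; 71% for 9 AHWs and 57% for 3 at ρ = 0.04, all attending). Without any continuity correction the baseline is 85.5%. With all attending, power is then 84%, 82% and 79% for 9 AHWs, and 81%, 76% and 70% for 3.

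**Standard errors.** Take equal outcome variance under the null and a test that models OM but not AHW. The true standard error exceeds the modelled one by r = √[(1.11 + D)/(2 × 1.11)], and the actual size of a nominal 5% test is 2[1 − Φ(1.96/r)]. At ρ = 0.04 with all attending, 9 AHWs give r = √(2.71/2.22) = 1.11 and a size of about 8%; 3 AHWs (D = 1.11 + 39 × 0.04 = 2.67) give r = √(3.78/2.22) = 1.30 and about 13%.

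**The case against.** The strongest reply is that the premise is not in the text. A reader might infer that a small pool of AHWs serves many OMs each and conclude that the 80% power fails. The article gives no AHW count, caseload or mapping to OMs, and a condensed article may leave that staffing detail to the full protocol. The inference is reasonable: 160 × 20 minutes is about 53 hours of counselling at most, and a separate recruited specialist for each of 32 OMs is hard to imagine. It remains an inference.

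Three further points stand in part.
- The 0.04 is a primary-care value chosen for clusters of about 3. It is not an estimate of counsellor variation in one protocol-based session by staff trained to a standard. The ICC therefore has to be shown as a range.
- Only attenders meet the AHW, and every BLC client also receives the OM's advice and the leaflet. Half attendance removes much of the loss, as the table shows.
- Without continuity correction, power stays at or above 80% in many scenarios. But the plan's 109 rests on that correction, so its stated 80% has to be judged on the same method.

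Finally, which random effects enter the model is commonly settled in an analysis plan, and one may exist that includes the AHW. The missing model term alone would therefore not be a finding. An analysis plan would not alter the sizing statement printed here, which applies one OM-type factor to an arm with a second provider.

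**Conclusion.** The point holds in conditional form. The sizing covers OM-type clustering only and applies it equally to all arms, and on the plan's own method nothing is left over. The 80% for BLC v leaflet is therefore supported only if AHW clustering is negligible. Under the assumptions shown (3 or 9 AHWs, ICC 0.01 to 0.04) power is about 60 to 78% with full attendance and 74 to 80% with half. With many AHWs, a small ICC or low attendance, the loss is a few points at most.

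Three stronger readings are not supported. The documents do not establish that the 80% fails, since that depends on three unstated quantities. They state no target interval width, so none is missed. They state no power for BLC v brief advice, because the 13-point difference is for brief intervention against control. For that contrast the point concerns standard errors only. The false-positive figures of 8% and 13% likewise apply only if the final model omits the AHW.

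**What to change.** 1. **Data.** Record the AHW linked to each BLC client or OM by referral, whether or not the client attended, so that the analysis remains by intention to treat. This linkage may be hard to recover later.
2. **Planned analysis.** Estimate the BLC contrasts from a mixed logistic model with an OM random effect in all arms and an AHW random effect in the BLC arm only, with a small-sample correction. If there are too few AHWs to estimate the variance, report this model as a prespecified sensitivity analysis.
3. **Sample size calculation.** State that the 80% allows for OM clustering only. Give BLC v leaflet power as a range over AHW ICC and attendance, using the actual number of AHWs, and not as one figure.

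The cost is one extra recorded field and some redrafting, with no extra clients. The downsides are a somewhat wider BLC interval, an imprecisely estimated AHW variance and a less favourable stated power for BLC v leaflet.

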### Planned analysis

As the study is pragmatic in design, the planned analysis will be by intention to treat. The primary outcome is dichotomous in nature, drinking within or above recommended levels, and will be analysed with logistic regression adjusting for all known prognostic factors; data will be presented as odds ratios and their corresponding confidence intervals. Secondary analyses will be undertaken using the appropriate method for the outcomes, controlling where appropriate for intake values and other known prognostic variables using analysis of covariance.

Due to the nested factorial nature of the study, we will use multi-level modelling to explore potential interactions between each of the levels nested within the trial (screening method and intervention). Offender manager and offender factors will be utilised as part of regression model to explore possible prognostic factors that impact on outcome. Interaction analysis will explore any possible interactions between site and offender characteristics and outcome.

The efficacy of interventions will be explored using a per protocol approach to the analysis. A sub-group, of those who received their allocated treatment will be utilised for this analysis.

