### Design

The trial will adopt a 2 × 3 nested factorial design encompassing screening method (the Fast Alcohol Screening Test (FAST) [28] or a modified Single Alcohol Screening Questionnaire (M-SASQ)) [29]) and brief intervention intensity (Client information leaflet (CIL); Brief advice (BA); Brief lifestyle counselling (BLC)). The main advantages of utilising a factorial approach are twofold. First each of the elements (screening tool and intervention) can be analysed independently with sufficient power to make meaningful interpretation of relative effectiveness. Second, the method enables meaningful interpretations of the relative effectiveness of any screening tool and intervention modality.

The 96 recruited OMs will be randomly assigned to 1 of 2 screening tools (48 OMs using each tool) and 1 of 3 intervention conditions (32 OMs in each condition) as shown in Table 1. Since we expect that there may be a difference in uptake of screening between intervention conditions, we expect the recruitment to take varying periods of time in the different conditions.

**Table 1 T1:** SIPS CJS trial design

	Intervention allocation				Total
		**PIL**	**BA**	**BLC**	
	
		OMs = 16	OMs = 16	OMs = 16	OMs = 48
**Screening allocation**	**FAST**	Participants = 80	Participants = 80	Participants = 80	Participants = 240
	
	**M-SASQ**	OMs = 16	OMs = 16	OMs = 16	OMs = 48
		Participants = 80	Participants = 80	Participants = 80	Participants = 240

		OMs = 32	OMs = 32	OMs = 32	OMs = 96
**Total**		Participants = 160	Participants = 160	Participants = 160	Participants = 480

The trial will incorporate cluster randomisation of OMs to avoid the risk of contamination. OMs trained to deliver brief advice become compromised in their ability to deliver alternative versions of such care; thus it is not practical for individual OMs to deliver both control and intervention conditions in this trial. Therefore OMs will consistently deliver one particular type of brief intervention.

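### As stated, the primary logistic model makes no allowance for clustering by Offender Manager, although the trial randomises Offender Managers and is sized for clustering

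*Protocol article*

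**What the plan says.** All quotes are from the protocol article.

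- **Unit of randomisation (Design).** "The trial will incorporate cluster randomisation of OMs to avoid the risk of contamination". Table 1 shows 32 OMs and 160 participants in each intervention condition.
- **Sample size calculation.** "The proposed study involves a cluster design and requires a statistical adjustment to account for any potential cluster effect". The section then sets the ICC: "Our experience leads us to assume the ICC should be similar to primary care correlation coefficients, 0.04". It goes on: "Assuming a cluster size of the order 3 offenders this inflates the sample size calculation by a factor of 1.1".
- **Primary model (Planned analysis).** The dichotomous primary outcome, drinking within or above recommended levels, "will be analysed with logistic regression adjusting for all known prognostic factors; data will be presented as odds ratios and their corresponding confidence intervals".
- **Multi-level modelling (Planned analysis, next paragraph).** Because of the nested factorial design, "we will use multi-level modelling to explore potential interactions between each of the levels nested within the trial (screening method and intervention".
- **OM variables (same paragraph).** "Offender manager and offender factors will be utilised as part of regression model to explore possible prognostic factors that impact on outcome".

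**The concern.** Offenders who share an OM share that person's screening practice and delivery of the intervention, so their outcomes may be correlated. The interventions are compared between OMs. A model that treats offenders as independent therefore understates the standard error of each intervention odds ratio.

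The sample size section accepts this and pays for it in recruitment. The Planned analysis section does not carry it through. The sentence that fixes the primary model lists covariates and nothing for OM. The one method that could hold a cluster term is given a different task. The levels named for it are screening method and intervention, which Table 1 shows to be two crossed randomised factors. The actual hierarchy is offenders within OMs within probation areas. OM characteristics do enter a regression, but as possible prognostic factors, and covariates of that kind do not replace a cluster term.

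A statistician who followed the section literally would fit a single-level primary model. At stake are the error rate of the main test and the coverage of the main intervals.

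**Working it through.** **Inputs**

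- From the Sample size calculation: success rates of 5% and 18%, two-sided 5% test, 80% power, 25% loss to follow-up, ICC 0.04, about 3 offenders per cluster, inflation factor 1.1.
- From Table 1: 160 participants and 32 OMs per condition, so 160/32 = 5 recruited per OM. After 25% loss, 5 × 0.75 = 3.75 are analysed per OM.

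**1. The plan's own figures**

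- Two proportions, 5% against 18%, with continuity correction: 109 per group, as stated (94 without the correction).
- Loss to follow-up: 109/0.75 = 145.3; the plan states 145.
- Clustering: 145 × 1.1 = 159.5, so 160 per group and 480 in total.

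The sample size reproduces and includes an allowance for clustering.

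**2. Effect of leaving clustering out of the primary model**

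Design effect DE = 1 + (m − 1) × ICC. The unadjusted standard error is 1/√DE of the correct one. The true two-sided error of a nominal 5% test is 2 × [1 − Φ(1.96/√DE)].

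| Offenders per OM (m) | DE at ICC 0.04 | Unadjusted SE / correct SE | True error | Coverage of nominal 95% interval |
|---|---|---|---|---|
| 3 (sample size section) | 1 + 2 × 0.04 = 1.08 | 0.962 | 0.059 | 94.1% |
| 3.75 (Table 1 after 25% loss) | 1 + 2.75 × 0.04 = 1.11 | 0.949 | 0.063 | 93.7% |
| 5 (Table 1, recruited) | 1 + 4 × 0.04 = 1.16 | 0.929 | 0.069 | 93.1% |

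The first two rows are the relevant ones. The third would apply only with no loss to follow-up.

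**3. Check by simulation**

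Beta-binomial outcomes, 32 equal clusters per arm, ICC 0.04, unadjusted pooled z test:

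- success rate 12%: rejection 0.061 with 3 per OM and 0.063 with 4;
- success rate 18%: 0.061 and 0.062;
- success rate 5%: 0.051 and 0.060. With practically no clustering the same test rejects in 0.043 and 0.047 at this rate, so clustering still adds about 0.01 to a test that starts below 5%.

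The simulations agree with the formula where events are not too rare. At 5% the result depends on the test. An unadjusted Wald test rejected in about 4% of runs (0.037 to 0.046), which hides the excess. A likelihood-ratio test rejected in 0.072 to 0.086.

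**4. Sensitivity to assumptions that the document does not fix**

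- ICC from 0.01 to 0.10 (assumed) with 3 to 3.75 per OM: true error 0.052 to 0.083.
- Unequal numbers per OM at ICC 0.04 (assumed distributions): about 0.07 to 0.08 at success rates of about 12% and above.

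**5. Does the correct analysis need more offenders?**

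Analysed per group: 160 × 0.75 = 120. Effective number: 120/1.08 = 111 or 120/1.11 = 108, against the 109 required. Without continuity correction, power at these values is about 86% and 85.5%.

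**The case against.** The strongest reply is that the text is silent on the level of the model and does not state an error. A random-intercept model or a GEE with a logit link is also logistic regression, and it also yields odds ratios with confidence intervals. The article condenses a fuller protocol, and an analysis plan may specify the cluster term. The document plainly knows that it describes a cluster trial, and it plans multi-level modelling in the same section. Both randomised factors are allocated to OMs, so a multi-level model of them would most naturally place offenders within OMs.

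Much of this stands. A reader might infer that the investigators intend an ordinary single-level regression, that clustering will be ignored, and that the published intervals will be too narrow. The documents do not support that: no sentence calls the model single-level or says clustering will be left out. Nor is it true that the unadjusted 5% test would always be too liberal, since a Wald test near a 5% success rate is not.

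Omitting the stratifier does not support the point either, because leaving out a stratification factor generally makes inference conservative. How many prognostic factors to adjust for, and which unit to resample in the cost bootstrap, are separate questions that an analysis plan may settle.

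What the reply does not remove is the assignment of methods. The article goes beyond silence: it names a method for the primary comparison and gives the hierarchical method another purpose. That wording conflicts with the adjustment that its own sample size section calls necessary.

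**Conclusion.** The concern holds in limited form. The primary model, as stated, contains no allowance for clustering by OM, multi-level modelling is assigned only to interactions, and this does not match a sample size built on an ICC of 0.04.

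If the model were run as written, standard errors would be about 4 to 5% too small and the true two-sided error about 0.059 to 0.063. This rests on the plan's ICC, equal clusters of 3 to 3.75 analysed offenders, and the normal approximation. The effect is modest because the clusters are small. It would be larger with unequal clusters or a higher ICC. Both are assumptions, although the sample size section itself says the literature gives no clear ICC for this population. The point merits correction because it concerns the primary inference of a cluster-randomised trial and the remedy is simple.

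**What to change.** State in the Planned analysis section that the primary odds ratios and confidence intervals come from a logistic model that allows for clustering by OM. Either a random intercept for OM or a GEE clustered on OM with a small-sample correction would serve. The two estimate slightly different odds ratios, so name one as primary. Include intervention (three levels), screening tool (two levels) and the stratifier, probation area, as terms. If a full protocol or analysis plan already says this, align the wording with it.

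The cost is a change of wording and slightly wider intervals: by a factor of √1.08 = 1.04 to √1.11 = 1.05 at the plan's ICC. Recruitment need not change, because the 480 offenders already include the cluster inflation.

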## Interventions

### Client information leaflet

OMs randomised to the control condition, participating staff will be trained to screen eligible clients for hazardous or harmful drinking. Clients who screen positive and provide consent to participate in the study will complete the baseline questionnaire and then will be provided with a client information leaflet (CIL) http://www.sips.iop.kcl.ac.uk. The CIL to be used in this trial will be the Department of Health's "How much is too much; Drinking and You" leaflet [30]. This information booklet contains useful information about alcohol and includes the Drinkline telephone number where the client can access further information including treatment options for alcohol problems. Details of local alcohol services will also be attached to the back cover of the CIL.

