### Brief advice condition

OMs randomised to deliver Brief Advice, will be trained to screen eligible offenders for hazardous or harmful drinking. Offenders who screen positive and provide consent to participate in the study will complete the baseline questionnaire and will then receive up to five minutes of simple structured brief advice from trained OMs using the SIPS Brief Advice tool "Brief advice about alcohol risk" which has been developed for the purpose of the SIPS programme. It is based on the "How much is too much?" Simple Structured Advice intervention tool, developed as part of the UK version of the Drink-Less Brief Intervention programme [31] from a prototype used as part of a World Health Organisation collaborative study on alcohol screening and brief intervention [32]. Offenders in this condition will also receive a Client Information Leaflet (CIL) from the OM at the end of the brief advice.

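### The exploratory per-protocol efficacy analysis selects on attendance that only the counselling arm requires, so its BLC contrasts lose the protection of randomisation

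*Protocol article*

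**What the plan says.** The Planned analysis section makes intention to treat the main approach ("the planned analysis will be by intention to treat") and then adds a second one: "The efficacy of interventions will be explored using a per protocol approach to the analysis". The set for this second analysis is fixed in one sentence: "A sub-group, of those who received their allocated treatment will be utilised for this analysis".

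The Interventions section describes delivery by arm:

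- **CIL:** the OM hands over the leaflet once the baseline questionnaire is done.
- **BA:** clients "will complete the baseline questionnaire and will then receive up to five minutes of simple structured brief advice from trained OMs", and also get the leaflet.
- **BLC:** clients "will then receive up to five minutes of simple structured brief advice from trained OMS" and get the leaflet, as in BA. They are then referred to an AHW at a later appointment: "The AHW will deliver a 20 minute brief lifestyle counseling intervention to offenders who attend the appointment at the probation office".

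The article gives no expected attendance at the AHW appointment, and says nothing on how attenders and non-attenders differ.

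**The concern.** Receipt is observed after randomisation. In the CIL and BA arms it needs nothing more from the client than being present when consent and baseline are completed. In the BLC arm, full receipt needs one further act, coming to the AHW appointment. Keeping only recipients should therefore leave CIL and BA almost whole and reduce BLC to its attenders.

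The first study hypothesis is that BLC is more effective than simple structured advice, and this is the contrast most exposed. If willingness to attend goes with readiness to change, and readiness goes with drinking within limits, a difference would appear under the label of efficacy even if the AHW session had no effect.

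**Working it through.** **Inputs from the document (Sample size calculation).** Success is 18% under brief intervention against 5% in control, a planned difference of 13 points. There are 160 clients per arm and 25% loss, so 160 × 0.75 = 120 are followed up per arm. The plan's figures reproduce. The two-proportion formula for 5% v 18% (two-sided 5%, 80% power) gives 109 per group with continuity correction and 94 without. Then 109/0.75 = 145.3 (stated 145) and 145 × 1.1 = 159.5 (stated 160). The present point does not alter the sample size.

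**Assumptions (not in the document).** The AHW session adds nothing, so BLC and BA both have 18% success overall. A proportion *a* of the BLC arm attends. Attenders succeed at rate pA and non-attenders at pN, with gap g = pA − pN.

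**Formula.** From a·pA + (1 − a)·pN = 18% it follows that pA = 18% + (1 − a)·g. The per-protocol difference, BLC attenders minus the whole BA arm, is (1 − a)·g. The true difference is 0, so all of this is bias.

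| Attendance a | Gap g (points) | pA | pN | Bias (points) |
|---|---|---|---|---|
| 80% | 8 | 19.6% | 11.6% | 0.2 × 8 = +1.6 |
| 70% | 8 | 20.4% | 12.4% | 0.3 × 8 = +2.4 |
| 50% | 12 | 24.0% | 12.0% | 0.5 × 12 = +6.0 |
| 40% | 16 | 27.6% | 11.6% | 0.6 × 16 = +9.6 |

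**Second parameterisation.** Let r = pN/pA, so pA = 18%/(a + r(1 − a)). The rejection rate is for a two-sided 5% test of 120·a BLC clients against 120 BA clients, ignoring clustering.

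| r | a | pA | Bias (points) | Odds ratio | Rejection |
|---|---|---|---|---|---|
| 0.5 | 40% | 18/0.70 = 25.7% | +7.7 | 1.58 | about 21% |
| 0.5 | 60% | 18/0.80 = 22.5% | +4.5 | 1.32 | about 12% |
| 0.5 | 80% | 18/0.90 = 20.0% | +2.0 | 1.14 | about 7% |
| 1 | any | 18.0% | 0 | 1.00 | 5% |
| 1.25 | 40% | 18/1.15 = 15.7% | −2.3 | 0.85 | about 6% |
| 1.25 | 80% | 18/1.05 = 17.1% | −0.9 | 0.94 | about 5% |

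The sign of the bias is the sign of the prognosis gap, which the document does not supply.

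**Complier estimate for BLC v BA.** On the risk-difference scale it is the intention-to-treat difference divided by *a*. In every row above that is 0/a = 0. If the intention-to-treat difference were 5 points, it would be 5/0.4 = 12.5, 5/0.6 = 8.3 or 5/0.8 = 6.3 points.

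**Precision.** Take 18% in both arms, 120 per arm, no clustering and a = 50%. The intention-to-treat standard error is √(2 × 0.18 × 0.82/120) = 0.0496. The complier standard error is 0.0496/0.5 = 0.099, a 95% half-width of about 19 points. The per-protocol standard error at the same attendance (g = 12 points) is √(0.24 × 0.76/60 + 0.18 × 0.82/120) = 0.065, a half-width of about 13 points. The narrower interval is centred on the biased value of +6.

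**The case against.** **Status.** Intention to treat is the planned analysis. The per-protocol analysis is only explored, and no sample size or decision in the article rests on it. This stands, and it limits the weight of the point.

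**Where exclusions fall.** A reader might infer that participants would be dropped almost only from the BLC arm. The article gives no delivery or attendance figures. System measures plans to count how many receive an intervention under each model, and one hypothesis expects intervention activity to vary with access to an AHW, so OM delivery is not taken as complete. Receipt might also be defined by arm in an analysis plan not shown here. If BLC receipt meant only the OM's advice and the referral, the selection would largely vanish, but the analysis would then say little about counselling. What stands is structural: only BLC needs a further visit.

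**Direction.** A reader might infer that the analysis must favour BLC. That requires attenders to have the better prognosis, which the article does not state. It measures readiness at baseline but does not link it to attendance.

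**Adjustment.** The figures above are crude. The primary model adjusts for known prognostic factors, and AUDIT and the Readiness Ruler are taken at baseline. Carrying these into the per-protocol model would remove part of the bias, though not selection on unmeasured factors. The article does not say that it will.

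**Remedy.** A reader might infer that a complier estimate could replace the whole per-protocol analysis. It cannot. For BLC v CIL with AHW attendance as the exposure, the exclusion restriction fails, because BLC non-attenders still receive brief advice. BA v CIL does not involve AHW attendance at all. Even for BLC v BA there are assumptions to defend. Training is to be adapted to the condition, so the brief advice may not be identical. OMs also recruit clients after being randomised, and the Design section expects screening uptake to differ by condition. The intention-to-treat analysis shares that last weakness.

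**Conclusion.** The point holds for an exploratory analysis, with moderate weight. As written, the rule selects on a post-randomisation event that, by the delivery design, can fail mainly in the BLC arm. The BLC contrasts in that analysis are therefore no longer comparisons of randomised groups, and calling the result efficacy claims more than it can show.

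The size is conditional. With attendance of 40–80% and attender advantages of about 8–16 points, all assumed, the spurious gain for BLC is roughly 2 to 10 points before adjustment, beside a planned effect of 13 points. It is zero under equal prognosis and negative if non-attenders do better. The document supports neither a definite direction nor a definite size. The planned intention-to-treat analysis is unaffected.

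**What to change.** 1. For BLC v BA, base the efficacy estimate on a complier average causal effect, with randomised arm as the instrument for AHW attendance and standard errors clustered by OM. On the risk-difference scale this is the intention-to-treat difference divided by the proportion attending.
2. State its assumptions: the same brief advice and leaflet in both arms, no AHW access in BA, and no differential recruitment by OMs after randomisation.
3. Do not apply it to BLC v CIL with AHW attendance as the exposure.
4. If any per-protocol comparison is kept, define receipt separately for each arm, report AHW attendance, adjust for baseline AUDIT and Readiness Ruler, and label the result non-randomised and exploratory.

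The cost is a change of wording and a little more analysis. Attendance has to be recorded in any case to form a per-protocol set that depends on it. The price is a wider confidence interval, about 19 against 13 points either side in the 50% attendance example.
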